Medical management of mandibular osteoradionecrosis using courses of hyperbaric oxygen (HBO) or repurposed drug combinations have been explored. Recent clinical trials indicate that hyperbaric oxygen, is largely ineffective in preventing [5] or treating [6, 7] ORN. A repurposed drug combination pentoxifylline-tocopherol-clodronate (‘PENTOCLO’) [3] has been proposed as a potential pharmacological action. The pentoxifylline-tocopherol combination is thought to reverse soft tissue fibrosis induced by radiotherapy [8]. Potentiation of this combination by clodronate is indicated for osseous lesions, such as ORN of the mandible [9], without resorting to surgical resection and reconstruction. The pathophysiology and potential therapeutic opportunities in ORN have been reframed in recent years, aligned with the use of PENTOCLO, as a fibro-atrophic process. This is thought to be mediated by reactive oxygen species (ROS), a progressively fibroblastic stroma and emphasising the role of TGF-B1 [10]. Pentoxifylline, previously used to treat peripheral vascular disease, has been shown to have in-vivo anti-TNF alpha effect, to increase erythrocyte flexibility, increase vasodilation and to have anti-inflammatory effects [11]. As a single agent pentoxifylline has demonstrated some beneficial effects in soft tissue necrosis and trismus and various functional/symptomatic effects after radiotherapy in breast and head and neck cancer survivors [12]. Tocopherol acts as a ROS scavenger and an inhibitor of TGF-beta1 and procollagen gene expression, but alone has proved ineffective in the management of radiation-induced fibrosis. Combining the two agents, and exploiting their apparently synergistic mechanisms, the combination of pentoxifylline and tocopherol has demonstrated benefit in placebo-controlled trials [8] of radiation fibrosis and necrosis, although appears to need at least 12 months of continuous treatment to avoid rebound. Data on osseous lesions such as mandibular ORN has suggested adding clodronate to inhibit osteoclasts, which may potentiate the effectiveness of the protocol and this current triple regimen (termed PENTOCLO) has been used increasingly since 2005 [3]. Clodronate is a first-generation, non-nitrogenous, oral bisphosphonate, which specifically is not associated with drug-induced osteonecrosis. Clodronate reduces osteoclast activity, decreases fibroblast and macrophage proliferation, and promotes bone formation by osteoblasts. This combination has shown promise in medical management of ORN, with the necrotic bone forming a sequestrum that is eventually shed, revealing intact underlying mucosa.

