#### Worsening ORN

For either arm A or B (or in patient preference phase), if ORN deteriorates to the point that medical management is no longer indicated, the patient will progress to surgical resection and reconstruction of necrotic bone. After this surgery, it is presumed that there will no longer be remaining necrotic bone to monitor on trial, so this will lead to discontinuation of the study and thus the decision will trigger the Study Completion Visit.

Additionally, patients may discontinue treatment for reasons including intercurrent illness, pregnancy, death, clinician-led assessment of patients’ condition, non-adherence, newly developed or previously unrecognised exclusion criterion.

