### Outcomes {12}

The primary outcome measure is time from randomisation to healing of ORN (without the need for surgery), as measured by:Clinical examination by confirming completely healed oral mucosaIntra-oral clinical photographsRadiographs

Conversely, patients who demonstrate failure of treatment as below will be treated as censored observations:Deterioration of ORN including fractureA clinical indication to intervene with mandibular resection and reconstruction

Thus, either the diagnosis of complete healing at 12 months or mandibular fracture or other clinical indication to progress to surgery within 12 months both constitute a primary endpoint for that patient. Other patients whose ORN persists without the need for surgery will also reach the primary endpoint at 12 months, and any change in grade of ORN will be recorded as a secondary endpoint (as below Table 2).

**Table 2 Tab2:** Secondary outcome measures RAPTOR trial

Objectives	Outcome measures	Time point(s) of evaluation
Efficacy:		
1. Deterioration of ORN	Time from randomisation to worsening of ORN as measured: • Extent of exposed bone measured in two dimensions as mm^2^ (and for some trial visits supported by clinical photograph with in-field ruler) and • Notani grade	Every 3 months following randomisation until end of trial for that patient
2. Patients’ analgesia and antibiotic use	• Drug and dose taken for pain relief in the 24-h period leading up to appointment • Days of antibiotic usage. Systemic antibiotics taken since last trial appointment (type, dose and number of days for each type)	Every 3 months following randomisation until end of trial for that patient
3. Patients’ anthropological measurements	Patient BMI (kg/m^2^) where kg is a patient weight in kilograms and m^2^ is their height in metres squared	Every 3 months following randomisation until end of trial for that patient
4. Severity of disease	Grade by “Osteonecrosis of jaw” within CTCAE v 5.0 2017	Every 3 months following randomisation until end of trial for that patient
5. Quality of life	Quality of Life (EORTC QLQ-C30 and QLQ-H&N35)	Every 3 months following randomisation until end of trial for that patient
6. Mandibular preservation	Mandibular preservation rate measured as the removal of mandibula following surgery (segmental resection, with or without reconstruction)	Every 3 months following randomisation until end of trial for that patient
Toxicity:		

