## Statistical methods

### Statistical methods for primary and secondary outcomes {20a}

The primary outcome is time to healing. Healing rates will be estimated using the method of Kaplan and Meier. Comparisons across treatment groups will be performed using a log-rank test. Further analysis adjusting for key demographic and clinical covariates will be performed using a Cox proportional hazards model. The primary analysis will be carried out on the full analysis set, which will be defined on the intention to treat principle, retaining patients in their initially randomised groups irrespective of any protocol violations. Analysis of the primary outcome will be assessed using 1-tailed 0.1 level, as is consistent with the type I alpha level used in the study design. The one-sided test is employed in order to limit sample size and in the light of previous systematic reviews where no detriment to healing from PENTOCLO has been reported. All analyses of secondary outcomes will use the nominal *p* < 0.05 level to determine statistical significance. Full details of all planned analyses will be specified in a statistical analysis plan, which is provided as Appendix 1 (supplementary data).

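### Censoring treatment failures makes Kaplan-Meier overstate the proportion healed by 12 months; the log-rank test stays valid for the healing hazard but does not test that proportion

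*Protocol article*

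**What the plan says.** - Outcomes {12} sets the endpoint: "The primary outcome measure is time from randomisation to healing of ORN (without the need for surgery"). It then says that "patients who demonstrate failure of treatment as below will be treated as censored observations". Two kinds of failure are listed: deterioration of ORN including fracture, and a clinical indication for mandibular resection and reconstruction.
- The next paragraph of the same section puts failures beside full healing at month 12: "mandibular fracture or other clinical indication to progress to surgery within 12 months both constitute a primary endpoint for that patient". Patients whose ORN merely persists are said to reach the primary endpoint at 12 months too.
- Worsening ORN: patients who progress to resection leave the study, because "it is presumed that there will no longer be remaining necrotic bone to monitor on trial".
- Statistical methods {20a}: "Healing rates will be estimated using the method of Kaplan and Meier", and "Comparisons across treatment groups will be performed using a log-rank test". A Cox model gives the adjusted analysis. The section names no competing-risk method.
- Sample size {14} plans on 12-month healing of 40% (control) v 60% (PENTOCLO), one-sided alpha 0.1, 90% power, 78 events and 120 patients.

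**The concern.** Read as an estimate of the proportion healed, Kaplan-Meier treats a censored patient as having the same future chance of healing as those still under observation. That is reasonable for someone who moves away. It is not reasonable for a patient sent to resection, whose chance of healing without surgery is gone. Removing such patients from the risk set pushes the estimated healing rate up, and more so in an arm with more failures.

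The sample size is stated in proportions healed, and Objectives {7} asks the trial for an effect size to inform a definitive trial. If the published healing rates are too high, or inflated unequally, that later trial is planned on the wrong figures. Sites are unblinded. The blinded panel reviews photographs and radiographs, and the article does not place the decision to operate, which triggers censoring, under blinded review.

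A second difficulty is the first failure bullet. Taken literally, it also censors a patient who worsens, stays in follow-up and could still heal.

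**Working it through.** **1. The plan's own figure.** Constant hazards with no failures give HR = ln(1 − 0.40)/ln(1 − 0.60) = 0.5108/0.9163 = 0.5575, stated as 0.56. Schoenfeld, one-sided: events = 4(1.2816 + 1.2816)²/(ln HR)² = 26.28/(ln HR)². This gives 77 with 0.5575 and 79 with 0.56, so the stated 78 reproduces. The step from proportion to hazard uses proportion = 1 − exp(−hazard), which holds only if nobody fails before healing.

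**2. What one minus Kaplan-Meier reads when failures are censored.** Let h be the true proportion healed and f the proportion failing by 12 months, with constant hazards of both.

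- Total cumulative hazard: T = −ln(1 − h − f).
- Healing share: T·h/(h + f).
- Kaplan-Meier reading: 1 − (1 − h − f)^(h/(h + f)).

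Example, h = 0.40 and f = 0.30: 1 − 0.30^(0.40/0.70) = 0.497. The values of f are assumptions.

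| Failure by 12 months | Reading, true 40% | Reading, true 60% |
|---|---|---|
| 0% | 40.0% | 60.0% |
| 5% | 41.2% | 62.1% |
| 10% | 42.6% | 64.4% |
| 20% | 45.7% | 70.1% |
| 30% | 49.7% | 78.5% |

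Cumulative incidence returns 40% and 60% in every row.

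The only figure in the article is in Background {6a}: 15 of 186 patients in a review of treated series had jaw resection, 15/186 = 8.1%. At f = 0.08 the readings are 1 − 0.52^(0.40/0.48) = 42.0% and 1 − 0.32^(0.60/0.68) = 63.4%.

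**3. Check by hand.** Of 100 patients, 10 heal at each of months 3, 6, 9 and 12, and 30 are censored for failure just after month 3. Kaplan-Meier unhealed = 0.9 × 50/60 × 40/50 × 30/40 = 0.45. It reads 55% healed when 40% healed.

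**4. The test.** Simulated with the model of step 2: 57 per arm (120 less 5%, halved), 5,000 trials, one-sided 0.1. *Censored* is the log-rank test as planned. *Kept at risk* holds failures in the risk set, unhealed, to 12 months.

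| Healed, control v PENTOCLO | Failed, control v PENTOCLO | Rejection, censored | Rejection, kept at risk |
|---|---|---|---|
| 40% v 60% | 0% v 0% | 0.81 | 0.81 |
| 40% v 60% | 30% v 10% | 0.60 | 0.80 |
| 40% v 60% | 20% v 10% | 0.76 | 0.82 |
| 40% v 60% | 20% v 20% | 0.91 | 0.84 |
| 40% v 40% | 20% v 20% | 0.11 | 0.11 |
| 40% v 40% | 10% v 30% | 0.29 | 0.11 |
| 50% v 50% | 10% v 30% | 0.40 | 0.13 |

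In the second row Kaplan-Meier reads 49.7% v 64.4%, and the hazard ratio is 0.67 rather than 0.56. In a simulation with visit-based healing times and about 8% failing in each arm (2,000 trials), power for 40% v 60% is 0.82 censored and 0.80 kept at risk, and rejection at 50% v 50% is 0.10 both ways.

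**5. The deterioration bullet against the rest of the text.** The bullet names deterioration including fracture. The paragraph after it restates failure as fracture or an indication for surgery, and carries patients who persist without needing surgery to 12 months, with change of grade as a secondary endpoint. Table 2 lists deterioration as a separate secondary outcome. Worsening ORN ends the study only for surgery. The bullet is therefore wider than the text around it. A patient who worsens and then heals is conceivable: Background {6a} describes healing through "the necrotic bone forming a sequestrum that is eventually shed, revealing intact underlying mucosa", though it does not call that course deterioration.

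**The case against.** **The log-rank test is not invalid.** This stands. A reader might infer from the 0.29 and 0.40 above that type I error is inflated. Those figures are rejection rates when the proportions healed are equal but the healing hazards are not, under assumed unequal failure. With healing and failure both equal, the test rejects at 0.11.

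**Keeping failures at risk has its own exposure.** This stands too. With identical healing hazards (50% net of failure) and net failure of 30% control v 10% PENTOCLO, the planned test rejects at about 0.10, and keeping failures at risk rejects at about 0.20. If unblinded clinicians operate sooner on controls, a cumulative incidence comparison favours PENTOCLO. Whether avoided surgery counts as benefit is a choice of estimand, so the documents do not support insisting that Gray's test become primary.

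**Failure may be rare.** Surgery is described as a last resort, entrants must be suitable for medical management without fracture, and the only figure is about 8%. At that rate the effect on the test is negligible and the inflation is about 2 to 3 points. But the 8% comes from treated series, and no control figure is given.

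**The endpoint wording is not a true contradiction.** A reader might infer that failures are counted as events as well as censored. Since persisting patients also reach the primary endpoint, the phrase most likely means the end of primary follow-up. The wording is loose, no more.

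**Lost healing events are not established.** The surrounding text suggests that worsening without surgery does not censor. What stands is an ambiguity in the rule for the primary endpoint.

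**The SAP may add competing-risk estimates.** It was not available here. The article itself nevertheless fixes both the censoring rule and the estimator.

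**Conclusion.** The concern holds for the estimate, and in a limited form for the test.

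- **Estimate.** With failures censored, one minus Kaplan-Meier overstates the proportion healed whenever failures occur, even if they are equally common in both arms. The excess is about 1 to 10 points at 40% healed and 2 to 19 points at 60%, for 5% to 30% failure.
- **Test.** The planned log-rank test is sound for the cause-specific healing hazard. It does not answer whether more patients heal by 12 months, which is how the trial is planned. If PENTOCLO prevents failure, as hoped, the gap hides benefit (power about 0.6 instead of 0.8 at 30% v 10%). If failure is commoner under PENTOCLO, equal proportions can be declared different.
- **Wording.** The deterioration bullet needs limiting, and the endpoint phrase needs clearer words.

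All sizes rest on assumed failure rates and, apart from the hand check and the visit-based run, on constant hazards.

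**What to change.** 1. Estimate 12-month healing by Aalen-Johansen cumulative incidence in place of one minus Kaplan-Meier. Resection or an indication for it, fracture leading to study exit, and death are competing events, counted as not healed.
2. State that deterioration without study exit does not censor, and that observation for healing then continues to 12 months.
3. State that the log-rank and Cox results concern the cause-specific hazard of healing. Report beside them a between-arm comparison of cumulative incidence (Gray's test, or the difference at 12 months) and the failure rates by arm. Choose the primary test from the trial's estimand, before the data are analysed.
4. Reword the phrase that failures and healing constitute a primary endpoint, so that it says they end primary follow-up.

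The cost is wording in the protocol and SAP and a little more analysis with standard software. Healing, deterioration and surgery are already recorded. Reported healing rates will be lower than Kaplan-Meier would show. Trial status says that recruitment is open and completion is expected in 2027, so the change can be made before analysis.

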### Objectives {7}

A rigorous evaluation of PENTOCLO in the management of ORN of the mandible is now necessary. The primary objective of RAPTOR is to determine if PENTOCLO triple therapy is effective in healing of mandibular ORN. This phase II trial is designed to establish the first robust signal of efficacy, an estimate of effect size, and the safety/tolerability of PENTOCLO in mandibular ORN. Additionally, a repository of blood samples from the trial will allow future studies to explore the genomic determinants of susceptibility to osteoradionecrosis [15, 16]. The results will also provide robust preliminary evidence on its efficacy and inform the feasibility and appropriateness of a subsequent definitive trial.

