### Intervention description {11a}

#### Arm A (control arm, standardised supportive care (SSC))

Arm A (control arm, standardised supportive care (SSC)) may include analgesia, mouthwash, antibiotics and alleviation of local trauma, and any other appropriate measures determined by the site clinician. It specifically excludes hyperbaric oxygen and operations including surgical resection of the mandible (rim or segment). Patients with loose or sharp bone sequestrae or teeth may receive minor debridement or extractions in the outpatient setting to alleviate trauma to the oral soft tissues. This may be with the aid of local anaesthetic as needed. This excludes more major surgery to excise bone that would be carried out in an operating theatre, using saws or drills, or requiring general anaesthetic. Placebo drugs are not used.

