7. Gastrointestinal tolerability of PENTOCLO regimen 2 weeks after commencing (Only in Arm B: PENTOCLO)	Gastrointestinal tolerability, as defined by CTCAE grading	2 weeks after commencing trial medications ± 5 working days, (may be by telephone)
8. Compliance	Evaluation of compliance to the IMP	Every 3 months following randomisation until the end of trial for that patient
9. Assessment of IMP’s combination safety	Evaluation of severe adverse events (severe AEs) and/or serious adverse events (SAEs) considered related to the study treatment	Every 3 months following randomisation until the end of trial for that patient
Exploratory:		
10. Patients’ pain and mouth function	• Pain • Eating • Mouth opening • Problems with teeth/gum • Painkillers used • Interference of these symptoms with patients’ daily activities	Every 15 days until end of trial (for that patient) Collected remotely on smartphone App

To avoid any potential risk of bias due to unblinded site investigators, OPT and clinical photographs taken with an in-field ruler (Puritan stick) are subject to a central blinded review. Training of site investigators is provided during site initiation visits and updates. In cases of trismus, clinical photographs are facilitated by intra-oral cameras which are available with disposable single use covers. Digital copies of the clinical photographs (with in-field rulers) are securely uploaded to the study database by the site staff. At the end of the trial, the central review panel will be provided with the anonymised clinical photographs by the Liverpool Clinical Trials Centre (LCTC) from baseline and 12 months (and at study completion for patients who continue beyond 12 months) for blinded assessment. The outcomes within the patient preference arm of the trial (i.e. after 12 months) will be considered and presented separately. Quality control of images and radiographs from each site is performed from the first images returned and a random sample thereafter.

The secondary outcomes measures include the determination of the impact of PENTOCLO on the deterioration of ORN, analgesia and antibiotic usage, quality of life (using EORTC QLQ-30), mandibular preservation, anthropological measurements, safety, tolerability and compliance of trial medications (complete list Table 2).

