### Concealment mechanism {16b}

Participants and site staff will be unblinded as to allocation.

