### Adverse event reporting and harms {22}

Adverse events will be reported up to the point of primary endpoint and continued for patients remaining within patient preference phase. All nonserious adverse events (AE)/adverse reactions (AR), whether expected or not, will be recorded in the relevant page of the case report form. Serious adverse reactions (SARs), serious adverse events (SAEs) and suspected unexpected serious adverse reactions (SUSARs) should be reported within 24 h of the local site becoming aware of the event. Further details over the trial procedures pertaining to SAE, SAR and SUSARs are provided in detail in the RAPTOR protocol, available at the RAPTOR trial webpage [17].

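### The declared safety outcome counts only events judged treatment-related, so in this open-label trial with a no-drug control it cannot give an unbiased between-arm comparison of harm

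*Protocol article*

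**What the plan says.** The Objectives section {7} lists among the aims of this phase II trial "an estimate of effect size, and the safety/tolerability of PENTOCLO in mandibular ORN". Table 2 in Outcomes {12}, which that section presents as the full list of secondary outcomes, has one general safety entry, item 9. Its objective is "Assessment of IMP’s combination safety" and its measure is "Evaluation of severe adverse events (severe AEs) and/or serious adverse events (SAEs) considered related to the study treatment", evaluated three-monthly until the patient leaves the trial.

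The control arm is supportive care alone, and for it the article says "Placebo drugs are not used". On blinding: "Participants and site staff will be unblinded as to allocation". The protection offered against that is confined to images: "OPT and clinical photographs taken with an in-field ruler (Puritan stick) are subject to a central blinded review".

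Collection is wider than item 9. The harms section {22} has all non-serious events recorded and SAEs reported, not only the serious reactions. The AE row of Table 3 runs from baseline through every contact and has no Arm B restriction. The ECG, blood count, clotting, renal, liver and calcium rows do carry a footnote limiting them to Arm B during follow-up.

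On the reporting window, {22} says: "Adverse events will be reported up to the point of primary endpoint and continued for patients remaining within patient preference phase".

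**The concern.** An outcome filtered on relatedness to the study treatment uses different effective definitions in the two arms when only one arm has a study drug. An Arm B event can be attributed to the drugs. The same event in Arm A has no trial drug to be attributed to. The filter is also a judgement, and no blinded review of causality is described.

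The error can go either way. Generous attribution in Arm B makes background illness in head and neck cancer survivors look like drug harm. Cautious attribution hides a real excess among that background. Only an all-cause comparison by arm avoids both, and randomisation has already paid for it. At stake is whether the trial's declared safety result can inform the later definitive trial, as {7} intends.

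**Working it through.** **1. The plan's own figure.** The article states no numerical target for safety. Its one design figure, 78 events for the primary outcome, reproduces by the Schoenfeld formula with one-sided alpha 0.1, power 90%, 1:1 allocation and hazard ratio 0.56:

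4 × (1.2816 + 1.2816)² / (ln 0.56)² = 78.16.

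The safety point does not depend on it. From Sample size {14} only the 120 patients are used, that is 60 per arm.

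**2. Who can contribute to item 9.**

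| Element | Arm A | Arm B |
|---|---|---|
| Trial drug or placebo | none | three drugs |
| AEs and SAEs collected (Table 3, {22}) | all-cause | all-cause |
| Follow-up ECG and blood tests (Table 3 footnote) | no | yes |
| Events able to meet the related filter, if study treatment means the trial drugs | about none | those so judged |

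The condition in the last row follows from item 9's objective, which names the combination of investigational drugs.

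**3. What the filter alone can do.** These are assumed rates, since the article gives none. Take 60 per arm, the same all-cause severe-event or SAE proportion r in both arms, a share q of Arm B events called related, and no Arm A events called related. The Arm B count is b = 60 × r × q, rounded, and Arm A is 0. With equal arms the two-sided Fisher p for 0 v b is 2 × C(60,b) / C(120,b), capped at 1.

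For r = 20% and q = 50%, b = 60 × 0.2 × 0.5 = 6, and p = 2 × (60·59·58·57·56·55) / (120·119·118·117·116·115) = 2 × 0.0137 = 0.027.

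| r (all-cause, A v B) | q = 10% | q = 30% | q = 50% |
|---|---|---|---|
| 10% (6 v 6) | 0 v 1, p = 1.00 | 0 v 2, p = 0.50 | 0 v 3, p = 0.24 |
| 20% (12 v 12) | 0 v 1, p = 1.00 | 0 v 4, p = 0.12 | 0 v 6, p = 0.027 |
| 30% (18 v 18) | 0 v 2, p = 0.50 | 0 v 5, p = 0.057 | 0 v 9, p = 0.003 |

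The true difference is zero in every cell, yet the item 9 count always favours Arm A. In two of the nine cells it crosses the nominal 0.05 level that Statistical methods {20a} sets for secondary outcomes. The article names no test for item 9, so the p-values only indicate scale.

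**4. What the all-cause comparison would offer.** With 60 per arm and two-sided 0.05, power is 33% for 10% v 20%, 24% for 20% v 30%, 67% for 20% v 40% and 79% for 10% v 30%. It is modestly powered, but free of attribution bias.

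**5. The AE window.** The harms section ends reporting at the primary endpoint, except in the preference phase. Item 9 runs until the patient's end of trial, and Table 3 collects AEs at each visit and at study completion. Outcomes {12} puts the primary endpoint at 12 months for healed and for persistent disease, but lets fracture or a surgical indication count earlier. For those last patients the statements need not give the same end date.

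**The case against.** Four points deserve weight.

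- **The data exist.** A reader might infer that the randomised comparison of harm is lost. The documents do not support that. {22} and Table 3 show all-cause AEs and SAEs collected in both arms, so the comparison is recoverable. It is missing only from the declared outcome.
- **The SAP may cover it.** All-cause AE tables by arm are routine SAP content, and nothing in the article rules them out. This stands as a limit on the consequence. It does not change the definition that Table 2 itself fixes.
- **The wording is ambiguous.** The relatedness clause might qualify only the SAEs, study treatment is not defined, and the article does not say who judges causality. So near zero in Arm A is a likely reading, not a certainty. Redefinition would settle each of these.
- **AE follow-up after healing.** A reader might infer from the harms section that AE reporting stops when a patient heals, so that follow-up is shorter in the arm that heals faster. The documents do not support that either. {12} places the diagnosis of complete healing at 12 months, Table 3 gives no exemption after healing, and item 9 runs to the patient's end of trial. What stands is a wording mismatch.

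A reader might also extend the point to item 7, "Gastrointestinal tolerability of PENTOCLO regimen 2 weeks after commencing (Only in Arm B: PENTOCLO". That item is openly a tolerability measure of the regimen in those who take it. Restricting it to Arm B is an ordinary choice, and no change is asked for.

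**Conclusion.** The point holds in a limited form. As worded, the only general safety outcome rests on a causality judgement with no described blinding, and the control arm can hardly contribute to it. It cannot serve as an unbiased randomised comparison of harm. This assumes that study treatment means the trial drugs and that unblinded site staff judge relatedness, as is natural in an open-label trial.

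The size cannot be fixed from the article. On the assumed rates above, equal all-cause harm shows as anything from 0 v 1 to 0 v 9. The primary analysis and sample size are untouched, and the all-cause data will be there. This is a free improvement to the plan, not a flaw that threatens the trial.

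**What to change.** - Reword Table 2 item 9 as all-cause severe AEs and all-cause SAEs, compared by randomised arm over the 12-month randomised phase, with treatment-related events as a descriptive subset.
- Add a note that follow-up laboratory and ECG findings are ascertained in Arm B only, so events detected solely by those tests are not comparable between arms.
- State the AE window once, reconciling the harms section {22} with Table 3 and item 9, including for patients who fracture or reach a surgical indication before 12 months.

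The cost is wording and table shells. No new data, visits or patients are needed.
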